### 2.7 Data collection

Demographic data [including age, sex, race, height, weight, and body mass index (BMI)] and baseline characteristics (including comorbidities, preoperative medications, baseline MAP and HR values, and ASA status) will be collected prior to the procedures. The primary and secondary outcome measures and other perioperative data will be documented by a trained independent investigator blinded to group assignment. All raw data will be recorded on the Case Report Forms. The lead investigator will be responsible for the completeness and accuracy of data.

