### 2.9 Sample size evaluation

The study is designed as a non-inferiority trial with a non-inferiority margin (δ) of 8% in terms of the success rate (Luo et al., 2022; Zhong et al., 2023). At a power of 80%, a one-sided alpha of 0.025, and assuming that the success rate of gastrointestinal endoscopy after fospropofol or propofol administration is both 95%, a total of 234 patients are calculated using PASS software (version 2021, NCSS, United States). Together with an anticipated drop-out rate of 10%, a total of 256 patients (128 patients in each group) will be required for this trial.

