### 2.10 Data management and statistical analysis

Statistical analysis in this trial will be performed using SPSS 25 (SPSS Inc., Chicago, Illinois, United States). Continuous variables are presented as the mean ± standard deviation (SD) or median with the upper and lower quartiles, whereas categorical variables are presented as frequencies and percentages. A P-value <0.05 is considered statistically significant. For the primary efficacy outcome, the difference in gastrointestinal endoscopy success rate between fospropofol and propofol groups and the corresponding two-sided 95% confidence intervals (CIs) will be calculated. Non-inferiority between fospropofol and propofol is concluded if the lower limit of the two-sided 95% CI of the difference in success rate between fospropofol and propofol groups exceeds the non-inferiority margin (−8%). The success rates of gastrointestinal endoscopy will be compared between the fospropofol and propofol groups using the Chi-square test or Fisher’s exact test. The Shapiro-Wilk’s test will be used to assess the data distribution. For comparison of secondary efficacy outcomes, the Cochran–Mantel–Haenszel (CMH) test or Fisher’s exact test will be used to compare the categorical variables between two groups, while a t-test (normal distribution) or Mann-Whitney U test (non-normal distribution) is used to compare continuous variables, as appropriate. The incidence of AEs and drug-related AEs between the two groups will be compared using a chi-square test or Fisher’s exact test. In addition, the further interaction analysis across the subgroups, including age (65–79 years vs. ≥ 80 years), history of cardiovascular, renal, hepatic, and pulmonary diseases (yes vs. no), as well as interventional therapeutic endoscopic procedures (yes vs. no), will be carried out using a logistic regression model to adjust the study outcomes for above-mentioned potential confounding factors. All randomly assigned patients who receive at least one dose of the study medication will be included in the full analysis set (FAS) according to the intention-to-treat (ITT) principle, and at least one evaluable efficacy outcome is used for the analysis of all efficacy outcomes and baseline characteristics of patients. The safety set (SS), which includes all patients based on the “as treated” principle, will be used for the analysis of safety outcomes. Since the anticipated protocol violation will be uncommon and missing data will be supposed to be missing at random, the interim analysis or imputation for missing data are not performed in this trial.

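### The logistic subgroup and adjustment model is too rich for about 13 expected failures, and it lists therapeutic procedure as a confounder although that may arise after randomisation

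*Protocol article*

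**What the plan says.** Section 2.10 (Data management and statistical analysis) adds, after the primary and secondary comparisons, an interaction analysis across subgroups. The factors are age (65–79 versus 80 or older), history of cardiovascular, renal, hepatic and pulmonary disease, "as well as interventional therapeutic endoscopic procedures (yes vs. no"). The analysis "will be carried out using a logistic regression model to adjust the study outcomes for above-mentioned potential confounding factors". The section does not say whether there is one joint model or one model per factor, whether disease history is four variables or one composite, or which outcomes are modelled. The Discussion extends the subgroup analyses to efficacy and safety, and presents the handling of confounding factors as a condition for reliable conclusions.

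Section 2.9 fixes the expected event count, "assuming that the success rate of gastrointestinal endoscopy after fospropofol or propofol administration is both 95"%, with 256 patients randomised.

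On timing, section 2.7 states that "baseline characteristics (including comorbidities, preoperative medications, baseline MAP and HR values, and ASA status) will be collected prior to the procedures". Therapeutic procedure is not named there or in Table 1. Section 2.3 has the allocation envelopes opened just before the endoscopy.

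The primary decision is separate. Section 2.10 concludes non-inferiority from the 95% confidence interval of the difference in success rates against −8%. The logistic model plays no part in it.

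**The concern.** Three features of this analysis look wrong.

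- **Too few failures.** A logistic model of success is informed by the rarer outcome, here the failures. If a subgroup-by-arm cell has none, the interaction odds ratio has no finite maximum-likelihood estimate, and Wald intervals and tests built on it are not usable.
- **A factor that may not be baseline.** Success under section 2.5.1 requires a completed endoscopy and limited top-up dosing. If the sedative, or failure to complete the endoscopy, influences whether a therapeutic procedure is done, conditioning on that procedure can distort the treatment effect.
- **The wrong rationale.** In a randomised comparison, baseline factors do not systematically confound the treatment effect. Testing for interaction and adjusting for covariates are different aims, and the section merges them.

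At stake is the reading of the subgroup results. Odds ratios of infinity or with enormous intervals, or a shifted adjusted effect, could be reported beside a sound primary result.

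**Working it through.** **Inputs from section 2.9.** Success is 95% in both arms, with "a non-inferiority margin (δ) of 8% in terms of the success rate". The error rates are "At a power of 80%, a one-sided alpha of 0.025". The total is 234 evaluable and 256 randomised (128 per arm). The documents give no subgroup prevalences, so those below are assumptions.

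**1. Reproducing the stated sample size.** Unpooled normal approximation, per arm:
n = (1.960 + 0.842)² × (2 × 0.95 × 0.05) / 0.08² = 116.5, rounded up to 117, so 234 in total. This matches the stated figure, so the 5% failure rate is the plan's own working assumption.

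**2. Expected failures.** 0.05 × 256 = 12.8, and 0.05 × 234 = 11.7. The 95% binomial ranges are 6 to 20 and 6 to 19.

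**3. Model terms, excluding the intercept.**

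| Reading of section 2.10 | Terms | Failures per term (of 12.8) |
|---|---|---|
| One factor at a time | 1 + 1 + 1 = 3 | 4.3 |
| Joint, composite history | 1 + 3 + 3 = 7 | 1.8 |
| Joint, four histories separate | 1 + 6 + 6 = 13 | 1.0 |

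**4. Empty cells, one factor at a time.** With m patients per arm in the subgroup and 128 − m outside it, and failures independent at 5%:
P(at least one of four cells has no failure) = 1 − (1 − 0.95^m)² × (1 − 0.95^(128−m))².

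| Assumed prevalence | m | 0.95^m | 0.95^(128−m) | P(at least one empty cell) |
|---|---|---|---|---|
| 50% | 64 | 0.038 | 0.038 | 0.142 |
| 30% | 38 | 0.142 | 0.010 | 0.279 |
| 15% | 19 | 0.377 | 0.004 | 0.615 |
| 10% | 13 | 0.513 | 0.003 | 0.764 |
| 5% | 6 | 0.735 | 0.002 | 0.930 |

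**5. Non-finite estimates by simulation.** 400 trials per scenario, N = 256, 5% failures independent of all factors. Assumed prevalences for age 80 or older, cardiovascular, renal, hepatic, pulmonary and procedure were: low 10/20/3/3/5/20%, middle 15/50/8/8/15/30%, high 30/50/30/30/30/50%.

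- Joint 13-term model: at least one non-finite coefficient in 100%, 98.5% and 67.5% of trials (low, middle, high).
- Joint 7-term model: 69% to 88% across scenarios.
- One-factor interaction models: 11% to 97%, depending on the prevalence, in line with step 4.

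**6. Common outcomes.** The Discussion cites about 30% for desaturation and hypotension under propofol. 0.30 × 256 = 76.8 events, or 5.9 per term with 13 terms. The 13-term model then separated in 87%, 21% and 0% of simulated trials (low, middle, high).

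**7. Therapeutic procedure.** Put side by side, section 2.3 places allocation before the endoscopy, and neither the pre-procedure list in section 2.7 nor Table 1 names therapeutic procedure, yet section 2.10 treats it as a confounder. Nothing shown establishes that it is fixed before treatment starts.

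**The case against.** The strongest reply is that the document does not commit to the worst model. A reader might infer a single 13-term regression whose estimates will be undefined. The text does not support that. Thirteen is an upper bound, the one yes/no label after the organ systems allows a composite, and models per factor are equally compatible. At prevalences of 30% to 50%, one-factor models usually give finite, though imprecise, estimates. A likelihood-ratio interaction test can also be computed when a cell is empty, so it would be too strong to call every interaction P-value meaningless. These points stand. They limit the claim to often non-finite or unstable, for sparse outcomes.

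A reader might also infer that therapeutic procedure is certainly a post-randomisation variable and that adjusting for it certainly biases the result. The documents do not say when therapy is decided. Some may be planned, and the list in section 2.7 is introduced as an inclusion, not as exhaustive. Bias requires that treatment or completion affect whether therapy is done, which is plausible but not shown. What stands is that the factor should not be an adjuster until its timing is fixed.

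Taken literally, the reference to study outcomes would put times and doses into a logistic model. Section 2.10 separately assigns a t-test or Mann-Whitney test to continuous outcomes, so this is loose wording and not a defect to press.

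Finally, the analysis is supplementary, and nothing says it would be used to bolster the main finding. That is correct and limits the severity. It does not make the stated method workable for the primary outcome.

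**Conclusion.** The point holds for the primary outcome and other rare outcomes. On the plan's own 5% failure rate there are about 13 failures in 256 patients, or about 12 in 234, for 3, 7 or up to 13 terms. Even with one factor at a time, the chance of an empty cell runs from about 14% at 50% prevalence to 93% at 5%. These figures rest on assumed prevalences and on failures unrelated to the factors. A higher failure rate than planned would ease the problem. Common adverse events are much less affected at moderate prevalences.

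Adjustment for therapeutic procedure may bias the treatment effect unless it is planned in advance. This is an inference from the order of events and the listed data, not something the protocol states. The confounding rationale is misplaced for baseline factors in a randomised trial. The non-inferiority conclusion rests on the confidence interval for the difference in success rates and is unaffected. The change should be made, but the trial's main result does not depend on it.

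**What to change.** Rewrite the subgroup sentences in section 2.10 as follows, and align the matching sentences in the Discussion:

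- For each subgroup, report the success-rate difference with a Newcombe or score 95% confidence interval, on the same scale as the −8% margin.
- If interactions are tested, take one pre-randomisation factor at a time, use Firth-penalised logistic regression for sparse binary outcomes, and label the analysis exploratory.
- State whether disease history is one composite factor or four.
- Do not adjust for therapeutic procedure unless planned therapy is recorded before randomisation.
- Remove confounding as the reason for the analysis.

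The cost is one reworded paragraph and its echo in the Discussion and, if planned therapy is kept as a factor, one case report form item before randomisation. The trial gives up adjusted P-values that would often be unreliable.

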
## 3 Discussion

Over the past decade, the volume of gastrointestinal endoscopic procedures has increased 10-fold (Xin et al., 2022; Song et al., 2023). Many patients now undergo esophagogastroduodenoscopy and colonoscopy during the same hospital visit, commonly known as same-visit bidirectional endoscopy. Same-day bidirectional endoscopy has been increasingly implemented because it reduces costs and facilitates decision-making for other interventions or treatments needed by patients (Laoveeravat et al., 2020). To improve patient comfort and facilitate these procedures, the use of sedation has been increasingly requested by patients (Dossa et al., 2021). Propofol is a sedative agent commonly used for sedation in gastrointestinal endoscopy (Grocott, 2018; Zhang et al., 2018). Although its pharmacological properties render propofol an almost ideal drug to achieve and maintain the desired level of sedation in gastrointestinal procedures (Stogiannou et al., 2018), it is not without its drawbacks, as adverse events such as respiratory depression, hypotension, and pain on injection have been reported (Sneyd et al., 2022). In previous studies of patients undergoing gastrointestinal endoscopy with propofol sedation, the incidence of desaturation and hypotension events was approximately 30% (Chiang et al., 2013; Eberl et al., 2020). In an analysis of national claims databases in France, Laanani et al. found that SAEs related to screening and diagnostic colonoscopies were more frequent in older patients, particularly those with comorbidities (Laanani et al., 2019). Furthermore, same-visit bidirectional endoscopy is a more complex and prolonged endoscopic procedure compared to a single either esophagogastroduodenoscopy or colonoscopy. Therefore, special considerations should be given for elderly patients received same-visit bidirectional endoscopy. Currently, the best sedation regimen to facilitate a same-visit bidirectional endoscopy in an effective, safe and satisfactory manner for both patient and endoscopist is still not clear (Song et al., 2023).

Fospropofol is a water-soluble, phosphate ester prodrug, which can be metabolized by alkaline phosphatases to release liberated propofol after intravenous administration (Garnock-Jones and Scott, 2010). The released propofol from fospropofol binds to the γ-aminobutyric acid (GABA) receptor and thereby potentiates GABA-inhibitory synaptic currents to induce sedative effects (Garnock-Jones and Scott, 2010). A study of its pharmacodynamic/pharmacokinetic relationship in 12 healthy volunteers found that an intravenous bolus 10 mg/kg dose of fospropofola achieved propofol plasma maximum concentration of 2.2 mg/mLafter 8 (range 4–13) minutes, and reached the minimum mean MOAA/S score of 1.2 after 7 (1–15) minutes. Participants in this study completely recovered from sedation after 21–45 min following fospropofol administration (Bengalorkar et al., 2011). As a new sedative, fospropofol is expected to have the same sedative efficacy as propofol in elderly patients undergoing same-day bidirectional endoscopy, with a lower incidence of adverse reactions caused by hemodynamic and respiratory depression than that of propofol. On bassi of a phase II dose-response trial in patients undergoing colonoscopy, fospropofol 6.5 mg/kg was determined as the ideal dose, as no recorded episodes of deep sedation occurred during procedures under this dose (Cohen, 2008). In addition, both physicians and patients mostly preferred for fospropofol 6.5 mg/kg over the other doses (Cohen, 2008). In two clinical trials, fospropofol was shown to be safe and well tolerated at an initial dose of 6.5 mg/kg intravenously with supplemental doses as moderate sedation for elderly, obese, and high-risk patients in minor surgical procedures (Gan et al., 2010; Bergese et al., 2013). Fospropofol disodium for injection is a prodrug that is metabolized into propofol to produce a general anesthetic effect when administered intravenously. A phase 3 trial demonstrated that fospropofol disodium was not inferior to propofol for general anesthesia induction in American Society of Anesthesiologists (ASA) physical status I-II adult patients undergoing elective surgery and reduced the incidence of pain at the injection site (Wu et al., 2021). In addition, fospropofol’s slower onset should have less impact on patient’s hemodynamics compared to propfol, although it may potentially slow patient recovery (Gan et al., 2010). In clinical conditions where a more prolonged effect is desired and immediate onset of action is less important, fospropofol may have advantages over propofol. A pilot study has shown that fospropofol, administered in either an infusion/bolus or infusion-only regimen, is tolerable and effective for the short-term induction and maintenance of sedation in mechanically ventilated intensive care unit patients (Candiotti et al., 2011). These findings have prompted to exploration of fospropofol in providing sedation for elderly patients undergoing same-day bidirectional endoscopic procedures. However, the role of fospropofol sedation for same-day bidirectional endoscopy in elderly patients has not been fully determined. To our knowledge, this will be the first randomized controlled trial to assess the efficacy and safety of fospropofol sedation for same-day bidirectional endoscopy in elderly patients. In our patients, an initial bolus dose of fospropofol 6.5 mg/kg in combination with sufentanil 5 μg will be used for sedation induction, followed by supplemental doses of fospropofol 1.6 mg/kg as needed to achieve target sedation levels. This strategy will minimize the risk of oversedation and associated complications. Moreover, several confounding factors, which can influence the study outcomes, must be appropriately managed in this study to ensure that the reliable conclusions are obtaine. Subgroup analyses of the efficacy and safety assessments will be performed on basis of age, interventional therapeutic endoscopic procedures, history of cardiovascular, renal, hepatic, and pulmonary diseases.

Several limitations must be pointed out in this study. First, our study will specifically include patients aged over 65 years with an ASA physical status I to III and a BMI between 18 and 30 kg/m^2^. Although these inclusion criteria will allow us to evaluate the anesthetic effect of fospropofol in this specific patient population, whether the conclusion from our study can be fully extrapolated to other elderly patients with higher ASA classifications or individuals with obesity warrants further investigation. Second, this trial don’t include different doses in the fospropofol group. We only evaluate 6.5 mg/kg fospropofol in combination with sufentanil for same-day bidirectional endoscopy in elderly patients because we intend to assess the efficacy and safety of fospropofol under the conventional effective dosage on basis of previous studies (Cohen, 2008; Bergese et al., 2013). The next step will be to investigate the dose-response relationship to establish optimal dosage of fospropofol sedation for elderly patients undergoing same-visit bidirectional endoscopic procedures. Finally, this study was a relative small sample, single center trial, and a prospective, multicenter trial with a larger sample size are needed to validate the preliminary results of this study. Despite these limitations, our study will provide valuable insights into the potential benefits of forpropofol-based sedation for same-day bidirectional endoscopy in elderly patients. Further research in larger sample size will be essential to determine optimal dosing regimens and extend the applicability of fospropofol to the broader patient populations undergoing same-visit bidirectional endoscopic procedures.

In conclusion, this prospective, randomized, double-blind, non-inferiority trial will verify the efficacy and safety of fospropofol sedation for elderly patients undergoing same-visit bidirectional endoscopy and confirm whether it is inferior to propofol. We believe that fospropofol represents a new option for sedation of elderly patients during same-visit bidirectional endoscopic procedures.
